### Secondary outcomes

#### ROM of the shoulder joint

ROM of the shoulder joint reflects its capacity to move in various directions and is an important indicator of functional performance. ROM is typically assessed using a goniometer (3). Normal values include: flexion (lifting the arm forward), 0–180°; extension (moving the arm backward), 0–50°; abduction (lifting the arm to the side), 0–180°; and adduction (bringing the arm toward the trunk), 0–40°. Internal rotation (rotating the arm inward) measures 0–70°, and external rotation (rotating outward) is 0–90°. Horizontal abduction (moving the arm away from the midline in the transverse plane) is 0–45°, and horizontal adduction (bringing it across the body) is 0–135°. These measurements are essential for evaluating joint mobility, identifying functional restrictions, and tracking progress during rehabilitation, particularly in patients with post-stroke shoulder pain.

#### The absolute vertical distance difference between the medial superior angle of the scapula on the affected side and the second thoracic spinous process (T2)

This measurement provides an objective assessment of scapular alignment on the affected side. Scapular malalignment is a common feature of PSSP, often resulting from stroke-related muscle imbalance, including weakness or spasticity. Common abnormalities include excessive elevation or downward rotation of the scapula, which can increase mechanical stress on the shoulder joint and contribute to pain and functional deficits. Measuring the vertical distance between the medial superior angle of the scapula and the T2 spinous process allows clinicians to quantify asymmetry and tailor postural correction strategies and therapeutic exercises accordingly (20). A visual reference for the measurement method is provided in Figure 8.

**Figure 8 fig8:**
[figure not shown]
Measurement diagram: medial superior angle of scapula to T2.

#### Musculoskeletal ultrasound

Musculoskeletal ultrasound is a practical and noninvasive method for detecting structural abnormalities commonly associated with PSSP. Key indicators include the distance from the acromion to the greater tuberosity of the humerus (Figure 9), effusion around the long head of the biceps tendon sheath (Figure 10), calcification in the supraspinatus (Figure 11) and subscapularis tendons, and increased thickness of the subdeltoid bursa (Figure 12). Effusion around the biceps tendon sheath often reflects inflammation or tendinopathy, which can contribute to pain and limited mobility. Calcifications in the supraspinatus and subscapularis tendons are typically associated with chronic rotator cuff conditions that result in impingement and reduced range of motion. Thickening of the subdeltoid bursa is suggestive of bursitis, a frequent source of discomfort in PSSP patients (21).

**Figure 9 fig9:**
[figure not shown]
Distance from the acromion to the greater tuberosity of the humerus.

**Figure 10 fig10:**
[figure not shown]
Effusion around the long head of the biceps tendon sheath.

**Figure 11 fig11:**
[figure not shown]
Calcifications in the supraspinatus.

**Figure 12 fig12:**
[figure not shown]
Thickness of the subdeltoid bursa.

Ultrasound examinations will be performed with the patient in either a seated or supine position, depending on the target structure. For the assessment of the long head of the biceps tendon, the patient will be seated facing the examiner with the shoulder in a neutral position and the forearm supinated, resting on the ipsilateral thigh. In the short-axis view, the transducer will be placed transversely over the anterior upper arm and moved proximally to identify the bicipital groove—an osseous depression between the greater and lesser tubercles of the humerus—where the long head of the biceps tendon is located. For the long-axis view, the probe will be rotated 90 degrees after identifying the tendon in the short axis. Scanning will continue distally to the musculotendinous junction and proximally into the glenohumeral joint space.

For the subscapularis tendon, the patient will externally rotate the arm to expose the tendon. From the short-axis view of the biceps tendon, the probe is moved medially into the lesser tuberosity region to obtain the long-axis view of the subscapularis tendon, which appears beak-shaped at its humeral insertion. Passive internal and external rotation of the shoulder may be used to dynamically assess the integrity of the tendon. For the short-axis view of the subscapularis, the probe is rotated 90 degrees from the long axis. The tendon may appear as multiple fascicles interspersed with hypoechoic muscle tissue; a comprehensive medial-to-lateral sweep will be performed to evaluate the entire tendon.

For supraspinatus tendon evaluation, a modified Crass position will be used. The patient will extend the shoulder posteriorly, flex the elbow, and place the dorsal hand over the posterior iliac wing on the ipsilateral side—roughly over the back pocket area. This positioning rotates the supraspinatus tendon anteriorly, allowing sagittal imaging over the greater tuberosity. The tendon will first be examined in the long-axis view, followed by a 90-degree probe rotation to visualize the short-axis view. The presence of calcific deposits will be recorded. The thickness of the subacromial-subdeltoid (SASD) bursa will be measured at its thickest point, and care will be taken to avoid excessive transducer pressure. In the neutral seated position with the arm relaxed at the side, the vertical distance between the acromion and the greater tuberosity of the humerus will also be measured.

For patients with limited mobility or severe pain, the standard Crass position may be modified to ensure patient comfort. In the traditional Crass position, the patient places the dorsum of the hand behind the back to touch the contralateral scapula, which helps tension the supraspinatus tendon and may reveal subtle tears. However, this posture may exacerbate discomfort in symptomatic patients and will be used cautiously.

Each ultrasound scan is conducted by two musculoskeletal ultrasound specialists who independently evaluate the images using a blinded assessment protocol. If both assessments align, the result is confirmed. In case of disagreement, the specialists discuss the findings to reach a consensus. If they agree following the discussion, the shared conclusion is accepted. If consensus cannot be reached, the sample is excluded and not used in the final analysis.

#### MBI

The MBI is a widely used scale for evaluating functional independence in activities of daily living (ADLs) in post-stroke populations. In patients with PSSP, MBI is especially relevant, as shoulder pain can significantly interfere with daily tasks such as grooming, feeding, and dressing. Lower MBI scores have been linked to higher levels of dependence and poorer functional outcomes in individuals experiencing post-stroke shoulder pain (22, 23). Research shows that PSSP often limits mobility and hampers basic self-care, with particular effects on dressing and walking. Monitoring MBI scores in these patients allows clinicians to assess the impact of pain on daily function and adjust rehabilitation plans accordingly to improve outcomes.

### Adherence

To support adherence and improve rehabilitation outcomes in patients with post-stroke shoulder pain, several structured measures are implemented during hospitalization: (1) A strict ward management system is maintained. All patients are required to stay within the rehabilitation ward to prevent interruptions in therapy, ensure continuity of care, and allow immediate medical response in case of complications or emergencies. (2) A daily attendance system is in place. Patients use a rehabilitation treatment card to check in for each session, which therapists sign after completion to verify participation. (3) Nurses play a key role in reinforcing adherence. They provide bedside education, distribute printed materials, and share instructional videos to help patients understand the significance of rehabilitation. Daily adherence checks are also conducted, during which nurses speak with patients to identify obstacles and suggest practical solutions. (4) The rehabilitation team delivers individualized multidisciplinary support. Physicians create tailored rehabilitation plans; therapists adjust treatment intensity based on patient tolerance; and nurses monitor progress closely. A weekly multidisciplinary meeting is held to evaluate each patient’s participation and make any necessary adjustments to their care plan. (5) Psychological support is integrated to maintain motivation and reduce resistance to therapy. Medical staff offer encouragement, share successful case examples, and involve family members for emotional reinforcement. For patients with low engagement, motivational interviewing techniques are applied to explore concerns, stress the importance of rehabilitation, and build confidence in the recovery process. Through this coordinated strategy, including ward restrictions, attendance tracking, regular monitoring, individualized care, and psychological support, patient adherence is actively reinforced, which contributes to better rehabilitation outcomes and higher standards of care.

### Safety

Throughout the intervention period, adverse events will be monitored weekly. An adverse event is defined as any unwanted experience occurring during the study. All such events will be recorded in the Adverse Event Case Report Form (CRF) to ensure consistent documentation and analysis.

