### Study intervention

Both the DPS therapy and SCTT were implemented concurrently to reduce variability caused by seasonal changes in symptom severity. During the four-week intervention phase, participants in both groups received manual therapy according to their assigned treatment. Each group underwent five therapy sessions per week, each lasting 40 min, for a total of four weeks. Participants remained in inpatient rehabilitation during this period, and weekly consultations were held to monitor adherence. The four-week treatment window reflects standard practice in China, where medical insurance typically limits inpatient rehabilitation to this duration.

Participants were instructed not to take nonsteroidal anti-inflammatory drugs (NSAIDs), including celecoxib, or acetaminophen during the trial. Medications such as celecoxib may pose risks for post-stroke shoulder pain patients with a history of cardiac stent placement, as they can impair platelet function and increase cardiovascular risk (7, 16). In cases of severe pain, acupuncture was used as a temporary alternative, integrated into the basic rehabilitation regimen. Routine rehabilitation therapy continued throughout the study to ensure uniformity in care delivery.

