Using a patient with right-sided post-stroke shoulder pain as an example, common postural deviations include lumbar spine lateral flexion toward the hemiplegic side, thoracic kyphosis, and scapular depression. The 4R technique is applied to correct these issues. The procedure involves the following steps: (1) With the patient in a seated position, the therapist stabilizes the left lumbar transverse process using one hand, while the other hand wraps around the proximal right upper limb, applying a gentle lateral pull to the left. This is performed 3–5 times. (2) To stretch the right lumbar muscles, including the quadratus lumborum and iliocostalis, the therapist stabilizes the right iliac crest with both hands while the patient actively bends the trunk to the left. The stretch is repeated 3–5 times. (3) The patient then bends the trunk actively to the right end range, holds the position for 8–10 s, and rests before repeating the motion 3–5 times. Once the movement is well controlled, balance disturbance exercises are introduced, such as applying light directional nudges or placing a balance cushion under the pelvis to stimulate proprioceptive response. (4) The therapist mobilizes the T1–T8 spinous processes using posterior-to-anterior techniques, repeated 8–10 times. Additionally, stretches are applied to the platysma, intercostal muscles, and upper rectus abdominis. Each stretch is held for 8–10 s and repeated 3–5 times. (5) Scapular mobilization is performed by stabilizing the axilla with one hand while the other hand mobilizes the inferior medial scapular edge in a medial-to-lateral and upward direction. Simultaneously, the pectoralis minor, subscapularis, and serratus anterior are stretched, each held for 8–10 s and repeated 3–5 times. (6) The humeral head is mobilized in multiple directions, superior, inferior, anterior, posterior, and rotational, within a pain-free range. Each direction is repeated 3–5 times. At the end of each movement, the patient is instructed to hold the final position, with assistance from the therapist if needed. (7) Finally, trigger points around the glenohumeral joint are compressed for 5–10 s, with pressure adjusted based on the patient’s tolerance. Refer to Figures 2–7 for specific procedural illustrations and schematic diagrams.

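### Adverse events get one scheduled check per five therapy sessions, and the daily nurse conversation and session card are not linked to their capture

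*Protocol article*

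**What the plan says.** The Safety section of the protocol article sets the frequency: "Throughout the intervention period, adverse events will be monitored weekly". Its definition is wide: "An adverse event is defined as any unwanted experience occurring during the study". All such events are to be entered on a dedicated adverse event CRF. No other timetable for seeking harms appears in the article.

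The Adherence section describes two more frequent contacts. The first is tied to each session: "Patients use a rehabilitation treatment card to check in for each session, which therapists sign after completion to verify participation". The second is tied to each day: "Daily adherence checks are also conducted, during which nurses speak with patients to identify obstacles and suggest practical solutions". Their stated purposes are attendance and adherence. Neither is described as an occasion to ask about, or record, adverse events.

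**The concern.** Both arms receive hands-on treatment every weekday, and the likely reactions are short-lived. The tuina regimen deliberately aims for a sore, full feeling at the points treated, works on tender areas, and goes on to traction and shaking. The DPS regimen compresses trigger points, mobilizes the humeral head in several directions and includes balance work: "balance disturbance exercises are introduced, such as applying light directional nudges or placing a balance cushion under the pelvis". A pain flare, bruising, dizziness or unsteadiness would be expected at or soon after a session and could settle before the next weekly check.

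The definition counts such events, but the one scheduled enquiry is poorly timed to find them. At stake is how complete the safety data are. The Introduction motivates the trial partly by the need for low-risk treatment, and the two intervention sections claim safe delivery. A low event count from weekly checks would be weak support for either statement. With 24 patients per arm, each patient whose event is missed lowers the observed proportion by 1/24, about 4 percentage points.

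**Working it through.** The plan gives no figure for completeness of adverse-event capture, so there is none to reproduce. The check is a count of contacts, followed by a comparison of what each contact is for.

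**Inputs**
- Sessions: 5 per week for 4 weeks (Study intervention: "Each group underwent five therapy sessions per week, each lasting 40 min, for a total of four weeks").
- Scheduled adverse-event checks: 1 per week during the intervention (Safety).
- Participants: 48 (Study design overview), allocated 1:1 (Enrollment and the informed consent process), so 24 per arm.

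**Count per participant**
- Sessions: 5 × 4 = 20.
- Scheduled checks: 1 × 4 = 4.
- Sessions covered by each check: 20 / 4 = 5.
- Sessions with no scheduled check that day, even if every check falls on a session day: 20 − 4 = 16, and 16 / 20 = 80%.

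**Count for the trial**
- Sessions: 48 × 20 = 960.
- Scheduled checks: 48 × 4 = 192.

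**Contacts side by side**

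| Contact | Frequency | Stated purpose | Linked to adverse-event capture |
|---|---|---|---|
| Adverse-event monitoring | Weekly (4) | Harms | Yes |
| Session card signed by the therapist | Every session (20) | Attendance | Not stated |
| Nurse conversation | Daily | Adherence | Not stated |
| VAS | Weeks 0, 2, 4 and 8 | Primary outcome | Not stated |

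The VAS does not fill the gap. It is taken twice during treatment after baseline, and the Primary outcome section has patients mark their pain at that moment, so a flare that has settled between visits leaves no trace.

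These counts show how many sessions each scheduled enquiry must cover. They do not show how many events would be missed. That depends on the true event rate and on how many events reach the CRF between checks, and the article gives neither.

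**The case against.** The strongest reply is that weekly monitoring need not mean a one-week recall question. The Safety section wants every event on the CRF and does not bar entry when an event arises. A running log or a weekly review of ward notes would fit the wording equally well. The CRF and full protocol, not shown, may give the procedure. The weekly interval also contradicts nothing else in the article.

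This stands as far as it goes. A reader might infer that harms are sought only once a week and otherwise left to memory, but the text does not say so. A reader might also infer that patients go on through further sessions unobserved. The Adherence section points the other way: patients stay on the ward, partly to "allow immediate medical response in case of complications or emergencies", therapists tailor intensity to what the patient tolerates, and nurses follow progress. These are measures of clinical care, however, and none is described as systematic adverse-event ascertainment. The weekly interval is a stated rule, not a detail left out.

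A third tempting inference is that the trial could report both therapies as free of harm. Illustrative figures do not bear this out. Assume a true rate of 30% and capture of 50–80% of events; neither figure is in the documents. The recorded rate would be 0.30 × 0.5 = 15% to 0.30 × 0.8 = 24%. Even at 15%, the chance of no recorded event is 0.85^24 ≈ 2% in one arm and 0.85^48 ≈ 0.04% in both. Under-counting may affect both arms, and nothing in the article shows that it would bias the comparison.

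A last objection concerns the remedy. The treating therapist knows the allocation and delivers the therapy being judged. A yes/no question at sign-off could also count tuina's intended soreness as an event, mainly in one arm. This is right, and it is why the session card should not be the main source.

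**Conclusion.** The point holds in a limited form. The only stated schedule for seeking adverse events is one check per five sessions. The definition it serves includes brief and mild reactions, and more frequent contacts already exist but are not linked to adverse-event capture. Transient reactions after a session may therefore be under-ascertained in both arms.

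The size that can be stated is the contact count alone: 4 scheduled checks for 20 sessions, assuming exactly one check in each treatment week. The amount of under-counting cannot be estimated from the documents. That some reactions are short-lived is an inference from the techniques described, not a figure in the article. The primary outcome and its analysis are unaffected. The change is worth making because it is cheap and would make a low event count more credible.

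**What to change.** - Add one standard adverse-event question (yes/no, type, onset), worded identically in both arms, to the nurse's existing daily check, and make this the main source. The nurse does not deliver the therapy; the article does not say whether nurses are blinded, and the protocol should state it.
- Use the session card as a secondary prompt only.
- Transfer every positive answer to the adverse event CRF.
- Record the expected passing sensation during treatment separately from reactions that persist after the session, so that an intended effect of one therapy is not counted as harm in that arm.
- Keep the weekly check to reconcile the daily answers with the CRF, and state how events noticed between checks reach it.
- If patients have already been treated, start the question in both arms on the same date and report counts before and after that date separately.

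The cost is a short question at a contact that already takes place, with no new staff or visits. It would be asked 48 × 20 = 960 times if on treatment days only, or 48 × 28 = 1,344 times if on all 28 days of the four weeks. More minor events will need to be entered.

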## Discussion

This study presents a rigorously designed randomized controlled trial protocol comparing the efficacy of Discovery of Posture Secret manual therapy with Standardized Chinese Tuina Therapy in patients with PSSP. As a common and functionally disabling complication in stroke survivors, PSSP remains a challenge to effective rehabilitation. The trial’s design integrates both subjective and objective outcome assessments, with a particular emphasis on incorporating musculoskeletal ultrasound to enhance the objectivity and clinical relevance of the evaluation process. The combination of a novel intervention approach and a multimodal outcome framework represents a comprehensive strategy to address this complex condition.

While SCTT remains a widely practiced and guideline-supported therapy for shoulder pain in China, it is primarily focused on local muscle relaxation and relies heavily on therapist experience. In contrast, DPS introduces a structured, biomechanically informed manual therapy model aimed at restoring joint alignment, reactivating neuromuscular control, and enhancing postural stability. By systematically addressing joint malalignment, abnormal muscle recruitment, and proprioceptive deficits, DPS is expected to offer broader and more sustained functional benefits compared to conventional tuina. The structured nature of DPS may also contribute to improved reproducibility and standardization in clinical practice, a longstanding challenge in traditional manual therapy.

The outcome framework of this trial includes one primary and several secondary measures, designed to reflect both patient-reported symptoms and functional recovery. Pain intensity, measured by the VAS, serves as the primary outcome due to its direct relevance to patient experience and its sensitivity to change. Secondary outcomes such as shoulder joint ROM, scapular alignment (quantified by the vertical distance to the T2 spinous process), musculoskeletal ultrasound, and the MBI are essential for capturing improvements in joint function and daily living capacity. Together, these indicators provide a multifaceted understanding of how different therapeutic strategies impact recovery.

A notable innovation in this study is the use of musculoskeletal ultrasound as an objective and structural assessment tool. Traditional evaluations of PSSP have largely relied on subjective scales or clinical observation, often lacking precise anatomical insight. In contrast, musculoskeletal ultrasound enables visualization and quantification of structural abnormalities such as subdeltoid bursa thickening, calcifications in the rotator cuff tendons, effusion around the long head of the biceps tendon, and reduced acromion-to-greater tuberosity distance. These structural changes are closely linked to pain and dysfunction in PSSP, and their inclusion in the outcome set allows for a more granular evaluation of treatment effects. Moreover, blinded dual-sonographer image assessment and the use of inter-rater reliability analysis contribute to the scientific rigor and reliability of these imaging outcomes.

Beyond its role as a diagnostic and monitoring tool, musculoskeletal ultrasound may also provide insight into the underlying mechanisms through which manual therapies exert their effects. For instance, a reduction in bursal thickness or tendon effusion following DPS intervention may suggest not only symptom relief but also a genuine reversal of soft tissue inflammation or mechanical impingement (24). In this way, ultrasound imaging serves not only as a clinical endpoint but also as a potential biomarker of therapeutic response, paving the way for mechanism-based rehabilitation research.

From a biomechanical perspective, DPS offers a compelling theoretical framework for addressing the pathophysiology of PSSP. Abnormal postural patterns and joint malalignment—such as thoracic rotation, scapular depression, or glenohumeral instability—are common in stroke survivors due to neuromuscular imbalance and compensatory movement (19). The four core components of DPS—Resetting Joint Malalignment, Resetting Abnormal Muscle Function, Resetting Joint Stabilization, and Resetting Sensory-Motor Control—are designed to systematically correct these dysfunctions. By restoring normal scapulothoracic and glenohumeral relationships, DPS may reduce secondary impingement, redistribute mechanical loads, and re-establish efficient motor patterns. The integration of biomechanical correction with sensorimotor retraining is particularly relevant in stroke rehabilitation, where central and peripheral impairments often coexist.

Despite the methodological strengths of this study, several limitations must be acknowledged. As a single-center trial with a modest sample size and relatively short follow-up period, the generalizability of the findings may be limited. Although ultrasound provides objective structural information, its interpretation remains somewhat operator-dependent despite efforts to standardize procedures. Future studies should explore the use of dynamic ultrasound to further elucidate the biomechanical mechanisms underlying therapeutic response. Additionally, long-term multicenter trials are needed to evaluate the durability of DPS outcomes and to validate its application across different PSSP subtypes and patient populations.

In summary, this study protocol combines a novel biomechanical manual therapy with objective imaging-based outcome measures to explore a comprehensive treatment strategy for post-stroke shoulder pain. The integration of musculoskeletal ultrasound enhances methodological rigor and provides a structural window into treatment response, while the biomechanical foundation of DPS contributes to a deeper understanding of rehabilitation mechanisms. This trial is expected to inform both clinical practice and future research in post-stroke rehabilitation.
